### 2.3. Sample Size

The sample size was determined to detect significant changes in the effects of postural balance between FtF and TR groups after six weeks that are clinically relevant. Our proposed difference of equal to or greater than 1.5 units is based on data from previous studies [14,15,16]. A standard deviation of 1 cm^2^, an alpha of 0.05, and 80% statistical power were also considered. A 5% attrition rate was also considered, thus it was determined that a minimum of 8 participants in each group (total sample of 16) would be required. The sample size calculation was performed using GRANMO (Institut Municipal d’investigació Médica, Barcelona, Spain).

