## Abstract

**Background:** Several exercise methods with virtual reality devices have been used in treatments for older adults and patients with neurodegenerative diseases, although the mechanisms continue to be elucidated. The aim of this study is to establish the feasibility and effectiveness of a rehabilitation programme using low-cost virtual reality aimed at improving postural balance in older adults. It also seeks to compare low-cost virtual reality under two delivery modalities, telerehabilitation (TR) in elderly centres and face-to-face (FtF) in rehabilitation centres. **Methods:** The study is set up as a non-inferiority two-arm parallel triple-blind randomised controlled clinical trial. Sixteen persons aged 65 to 75-years-old will be included. Eighteen Wii therapy sessions (25–30 min) will be provided through both FtF (control group, *n* = 8) and TR (exposure group, *n* = 8), both with a Nintendo Wii balance board. Data will be collected at baseline (week 0), during the Wii therapy sessions (weeks 2, 4, and 6), and during the follow-up (weeks 8 and 10). The primary outcome will be the area of centre-of-pressure (CoP) sway; secondary outcomes will be medial–lateral and anterior–posterior velocity and standard deviation of CoP; and tertiary outcomes will be clinical measures: single-leg stand, timed up-and-go tests, Barthel Index, and Tinetti’s scale. Statistical analyses will be performed using SPSS 20.00 for Windows. The trial adheres to the Declaration of Helsinki and the Chilean laws of rights and duties of the patient and research in humans. Ethical approval was obtained from the Ethics Committee of the University of Talca. Written informed consent will be obtained from participants. **Discussion:** In this trial, older adults from a Chilean city with a large rural and underserved population share will be included to test the feasibility and effectiveness of a rehabilitation programme using low-cost VR aimed at improving postural balance to generate evidence to support decision makers generating public health policy. **Trial registration:** Australian New Zeeland Clinical Trials Registration (ACTRN12621001380886).

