## 2. Method

### 2.1. Design

This is a non-inferiority randomised, triple-blind, controlled clinical trial. Reporting follows Standard Protocol Items: Recommendations for Interventional Trials (SPIRIT [39], see Supplementary File). Figure 1 provides an overview of the trial design. 

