### 2.8. Allocation

Participants will be randomly assigned to either the control (FtF) or experimental group (TR) with 1:1 allocation as per a computer-generated randomization schedule stratified by site and the baseline score of the Action Arm Research Test using permuted blocks of random sizes. For concealing treatment allocation, the block sizes utilised in this study will not be divulged. This statistical approach, tailored to the randomised and block design, has been adopted to ensure the practicality and cost-effectiveness of conducting the clinical trial.

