## 3. Discussion

Anticipated findings from this trial suggest that the TR modality will exhibit non-inferior effectiveness to the FtF modality, as evaluated through clinical and posturographic assessments. This expectation draws support from preliminary evidence surrounding the implementation of TR and VR interventions in different settings. According to a recent systematic review, telemonitoring and telerehabilitation were the most used methods of telecare interventions in older populations. The findings from various studies indicated that these interventions had a positive impact on different dimensions of quality of life, particularly in older adults. Evaluating the impact of telecare interventions can provide valuable insights for system developers to improve the effectiveness of current and future telecare technologies to better meet the needs of users, particularly older adults. Future research can focus on evaluating the impact of specific telecare systems on targeted populations using diverse research methodologies. This can help in understanding the effectiveness of telecare interventions in different settings and for different populations and guide the development and implementation of telecare technologies that are tailored to specific user requirements [51]. Similarly, telehealth occupational therapy has been widely utilised for older adults, with a focus on providing convenient occupational assessment and intervention for both occupational therapists and their elderly clients. Telehealth occupational therapy also allows for monitoring of patients’ activities and provides rehabilitation counselling and health education to older adults and their caregivers, resulting in improved home life security and efficacy of occupational therapy interventions. Particularly during the COVID-19 pandemic, telehealth has emerged as a valuable alternative to face-to-face modalities, ensuring continuity of care while minimizing risks of infection [52].

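### The 80% power in section 2.3 is power to detect a 1.5-unit difference between modalities, not power for the non-inferiority question the trial declares

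*Protocol article*

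**What the plan says.** The design is declared twice: "The study is set up as a non-inferiority two-arm parallel triple-blind randomised controlled clinical trial" (Abstract) and "This is a non-inferiority randomised, triple-blind, controlled clinical trial" (2.1. Design). The expected conclusion matches this label, namely that "the TR modality will exhibit non-inferior effectiveness to the FtF modality" (3. Discussion).

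Section 2.3 sets a different target: "The sample size was determined to detect significant changes in the effects of postural balance between FtF and TR groups after six weeks", with the changes in question described as clinically relevant. The effect size follows: "Our proposed difference of equal to or greater than 1.5 units is based on data from previous studies". The remaining inputs are: "A standard deviation of 1 cm^2^, an alpha of 0.05, and 80% statistical power were also considered". A 5% allowance for attrition then leads to a minimum of 8 per group, 16 in all. The section does not call 1.5 a margin and does not say whether alpha is one-sided or two-sided.

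Section 2.11 compares the groups with a t-test or Mann–Whitney U test, framed as tests of difference with significance at p ≤ 0.05.

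**The concern.** Power belongs to a hypothesis. In a test of difference, 80% power means an 80% chance of declaring TR and FtF different if they truly differ by the stated amount. In a non-inferiority trial, it means an 80% chance of excluding a TR deficit as large as the margin when the true difference is as assumed, usually zero. Section 2.3 states the first and the rest of the article claims the second.

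What is at stake is the weight the result can bear. The Abstract and Conclusions say the trial should inform public health policy. With 16 people, a non-significant test of difference is likely even if TR is materially worse, and the stated 80% could be taken as support for reading such a result as non-inferiority.

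**Working it through.** **Inputs.** From 2.3: difference 1.5 units (taken as cm², the unit of the SD), SD 1 cm², alpha 0.05, power 80%, attrition 5%, 8 per arm. From 2.8: 1:1 allocation. From 2.6.1: a larger sway area is worse, so a TR deficit is a larger mean area under TR. Not given in the article and therefore assumed: the margin, the sidedness of alpha, and a true difference of 0.

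**Step 1: reproduce the plan's figure.** For a two-sided test of difference with the normal approximation:

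n per arm = 2 × (1.96 + 0.84)² × (1/1.5)² = 6.98, rounded up to 7. Then 7/0.95 = 7.4, rounded up to 8. This matches.

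Two other routes also lead to 8:
- Non-inferiority with margin 1.5, true difference 0 and one-sided 2.5% uses the same formula, so it gives 7, then 8.
- A one-sided 5% calculation with the noncentral t distribution needs 7 per arm (84.1% power), then 8.

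The number alone does not show which calculation was run. The wording of 2.3 does: it sets out to detect a difference.

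**Step 2: non-inferiority power with 8 per arm.** The standard error is 1 × √(1/8 + 1/8) = 0.5 cm² on 14 degrees of freedom. The noncentrality is margin/0.5. Power is the probability that a noncentral t exceeds the critical value, which is 2.145 at one-sided 2.5% and 1.761 at one-sided 5%. The last column is the normal-approximation n for 80% power at one-sided 2.5%, before and after 5% attrition.

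| Assumed margin (cm²) | Power, one-sided 2.5% | Power, one-sided 5% | n per arm, before / after attrition |
|---|---|---|---|
| 1.5 | 79.7% | 88.6% | 7 / 8 |
| 1.25 | 64.3% | 76.8% | 11 / 12 |
| 1.0 | 46.1% | 60.1% | 16 / 17 |
| 0.75 | 28.7% | 41.4% | 28 / 30 |
| 0.5 | 15.2% | 24.4% | 63 / 67 |

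The margin that gives exactly 80% with 8 per arm is 1.51 cm² at one-sided 2.5% and 1.31 cm² at one-sided 5%. A true TR deficit lowers power further: with margin 1.5 and a true deficit of 0.5, the distance to the margin is 1.0, so the 1.0 row applies.

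**Step 3: precision.** The expected two-sided 95% confidence interval half-width is 2.145 × 0.5 = 1.07 cm². Even with an observed difference of zero, the trial would exclude only TR deficits larger than about 1.07 cm².

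**Step 4: the t-test as planned, for a difference of 1.5.** If alpha is two-sided, t-test power is 79.7% with 8 and 8, and 76.4% with 8 and 7. Expected losses at 5% are 0.05 × 16 = 0.8 of a person. Under the normal approximation, 7 and 7 still gives 80.1%.

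**The case against.** The strongest defence is that the two formulas coincide. If 1.5 cm² is read as the margin with no true difference, 16 people give 80% power for non-inferiority, and nothing in the arithmetic is wrong. That is correct, and it rules out one inference a reader might draw: that the figures can come only from a superiority calculation. They cannot show that, because three routes give 8 and sidedness is not stated. The defence still does not rescue the text. Section 2.3 presents 1.5 as a clinically relevant difference to be detected. Used as a margin, the same quantity would allow TR to be called non-inferior while losing what the plan treats as clinically relevant.

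A reader might also infer that the 80% is lost through attrition. The document does not support this. It did inflate for attrition, apparently from 7 to 8, and the formula that reproduces its n still gives 80.1% with 7 per arm. The small shortfall in Step 4 arises because a normal approximation was apparently used at very small n, and only if alpha is two-sided. At one-sided 5%, power is 86.4% with 8 and 7, and 84.1% with 7 and 7.

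Two further points are fair. The power figures depend on assumed margins, so both alpha conventions are shown. They are also unadjusted: the trial measures a baseline and plans a repeated-measures analysis, which could improve precision, but the article gives no correlation from which to calculate the gain.

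Finally, a full protocol or analysis plan might contain a margin. The point does not rest on its absence from the article. It rests on what 2.3 does state, which conflicts with the declared hypothesis.

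**Conclusion.** Wrong as written. The stated 80% power and 8 per arm are tied to detecting a clinically relevant difference of at least 1.5 units, while the trial is declared as non-inferiority and expects to conclude non-inferiority. Confidence in this mismatch is high, because it comes directly from the text.

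Its size depends on a margin the article does not give. With SD 1 cm², no true difference and an unadjusted t comparison, power is near 80% or above only at a margin of about 1.5 SD (about 1.3 SD at one-sided 5%). At a margin of 1.0 cm² it is 46% or 60%, and at 0.5 cm² it is 15% or 24%, for one-sided 2.5% and 5% respectively. The design can exclude only large TR deficits.

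**What to change.** At n = 16, rewrite section 2.3 to replace the 80% claim with:
- a non-inferiority margin for sway area, justified and smaller than the 1.5 cm² called clinically relevant;
- the assumed true difference between TR and FtF;
- the one-sided alpha;
- the non-inferiority power that follows with 8 per arm, calculated with the t distribution, and the expected confidence interval half-width (about ±1.07 cm² unadjusted).

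If the resulting power is low, state that the trial estimates the difference between modalities and cannot establish non-inferiority, and align the Abstract, 2.1 and the Discussion with that.

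This is a text change. Its cost is that the stated power becomes less favourable. Keeping 80% power at a smaller margin would instead need more participants, as the last column of the table shows.

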### 2.4. Eligibility Criteria

The considered inclusion criteria are: People aged 65 to 75-years-old (women and men), occasional or permanent corrected lens wear, Mini Mental State Examination (MMSE) score of over 24 points, and no falls history in the last 12 months. Exclusion criteria are vestibular impairment and/or access at home to a Nintendo Wii before the intervention. 

### 2.5. Interventions

The objective of this study is to evaluate and contrast the outcomes resulting from the implementation of affordable virtual reality technology across FtF and TR modalities. The low-cost virtual reality intervention entails the utilization of a Nintendo Wii balance board, facilitating the engagement of participants in four exergames.

The FtF group will receive training from a physiotherapist at the telerehabilitation centre of Universidad de Talca, specifically designed for elderly patients. In contrast, the TR group will be trained by an older adult who has undergone six months of training in the rehabilitation program using low-cost virtual reality. These trained older adults will act as therapists for their peers, who belong to two senior citizen centres located near their homes. These centres offer recreational and sports activities for older adults who attend daily. The elderly therapist will receive remote guidance from the telerehabilitation centre at Universidad de Talca, Chile.

FtF and TR groups will undergo a total of 18 sessions, which will be delivered over a period of 6 weeks, with a frequency of 3 times per week (Monday, Wednesday, and Friday) for 25 min per session, followed by four weeks of follow-up for the older adults. For the first 3 weeks, each participant will perform three sets of exercises with manual guidance and verbal instructions. Subsequently, only verbal instructions will be provided by a physiotherapist or elderly therapist. The rehabilitation program has three sets of exercises that improve postural balance in the sagittal, frontal, and transversal planes of motion. The games used in the first two sets of exercises are Snowboard, Penguin Slide, and Super Hula Hoop, while the Yoga game is used in the third set. In the first set of exercises, the older adults will stand in a relaxed position with their arms and hands at their sides. In the second set of exercises, each game will be repeated in a standing position with their hands on their waists. Between the first and second sets of exercises, a one to two minute break will be given, during which the participants will sit on a chair until they have recovered. The third set of exercises involves maintaining a relaxed posture during the Yoga game with their eyes open and then repeating it with their eyes closed.

To encourage adherence, all participants in both the FtF and TR groups will receive telephone reminders. At this stage, no modifications to the intervention protocols will be made throughout the study.

### 2.6. Outcomes

The trial will use posturographic and clinical measures to assess the differences in the effects of FtF and TR groups using low-cost virtual reality interventions for postural control. Posturographic measures assess postural control by measuring the centre-of-pressure sway, including variables such as sway area, trajectories, and velocity in the medial–lateral and anterior–posterior directions [40]. These measures have been shown to be sensitive to measure changes in postural control due to training in various populations, including young adults [41], patients with post-stroke hemiparesis [42], patients with Parkinson’s disease [43], and children with CP [44,45,46,47,48]. Clinical measures will also be used to assess changes in postural performance in the elderly. Participants will be assessed at baseline, the ends of weeks 2, 4, and 6, and at weeks 8 and 10 (post-intervention follow-ups) using both posturographic and clinical measures. Additionally, demographic and clinical characteristics of the study groups will be included.

#### 2.6.1. Primary Outcome

The present investigation will utilize the CoP sway area (CoP_area_) as a dependable and credible indicator of postural control across diverse clinical and nonclinical populations, as demonstrated by previous studies [40,41,42,43,44,45,46,47,48]. CoP_area_ serves as a comprehensive metric of the balance control system’s capacity to sustain a stable upright posture, and higher values of CoP_area_ signify suboptimal balance control.

#### 2.6.2. Secondary Outcome

As for the secondary outcome measures derived from the posturographic evaluations, the standard deviation and velocity of the CoP along the medial–lateral and anterior–posterior axes will be employed. The CoP standard deviation indicates the extent of variation in CoP displacements, while CoP velocity serves as an indicator of the capacity to adapt to postural changes, where higher values are indicative of suboptimal balance control. This is because delayed postural adjustments result in significant CoP displacement, necessitating swift corrections to ensure stability [40].

#### 2.6.3. Clinical Measurements Outcome

This study will use the Tinetti, single-leg stance, and timed up-and-go tests and the Barthel Index as clinical measurements, as described in a recent clinical trial [49]. It is interesting to note that these measures cannot identify fallers in the older adult population but are useful for identifying and tracking balance impairment in this population [50].

### 2.7. Recruitment

The study will recruit older adults from two Senior Citizen Centres in Talca, Chile, where the participants have little to no experience using a Nintendo Wii balance board. The recruitment process will be carried out by a team of experienced health professionals, including a physician and two physical therapists, who will screen potential participants based on the inclusion/exclusion criteria until the required sample size is achieved.

### 2.8. Allocation

Participants will be randomly assigned to either the control (FtF) or experimental group (TR) with 1:1 allocation as per a computer-generated randomization schedule stratified by site and the baseline score of the Action Arm Research Test using permuted blocks of random sizes. For concealing treatment allocation, the block sizes utilised in this study will not be divulged. This statistical approach, tailored to the randomised and block design, has been adopted to ensure the practicality and cost-effectiveness of conducting the clinical trial.

### 2.9. Management

At the beginning of the study, participants will be informed about their random assignment to either the FtF or TR group. To ensure engagement and compliance, older adults in both groups will be regularly asked about the content of the interventions they receive. Data entry will be conducted by an employee outside the research team, who will use separate datasheets to prevent researchers from accessing information about group allocation during data analysis.

The raw data will be stored electronically in encrypted text files, while the calculated and clinical outcome measures will be saved in an encrypted Excel spreadsheet. To ensure data security and prevent loss, backups will be created on a weekly basis.

### 2.10. Data Collection

All measurements will be conducted under identical conditions and by the same assessor at each time point, at a consistent time of day. Posturographic assessments (CoP displacements) for both groups will be obtained utilizing an AMTI OR67 force platform (Watertown, MA, USA). AMTI NetForce software (Watertown, MA, USA) will be utilised for the acquisition of moments and forces at a rate of 100 Hz. Data will be recorded, assigned a code, and saved on a personal computer. CoP variables will be determined using Matlab R2022 (Mathworks Inc., Natick, MA, USA).

All primary and secondary posturographic measures will be evaluated across eight distinct postural tasks, each lasting 60 s, except for the dynamic postural task which will last 30 s. The postural tasks will comprise two static conditions: (i) standing motionless with eyes open, and (ii) standing motionless with eyes closed. In addition, six dynamic conditions will be evaluated: voluntary sway in the mediolateral direction, following a metronome set at 30 Hz ((i) and (ii)) and 60 Hz ((iii) and (iv)), with eyes open and closed for each frequency. Multidirectional sway will also be assessed while playing two different videogames that challenge (v) anterior–posterior postural control (Snowboard, 30 s) and (vi) medial–lateral postural control (Penguin). It is anticipated that all assessments, including clinical evaluations, will be completed within 40 min.

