### 2.11. Data Analysis

Statistical analyses will be conducted using SPSS 20.00 for Windows. Descriptive statistics will be utilised to determine the demographic and clinical characteristics of participants in both groups (unpaired *t*-tests and χ^2^ tests). 

The normality and homogeneity of variance of all outcome measures will be assessed using the Shapiro–Wilk and Levene tests, respectively. If the assumptions of normality are met, a t-test will be employed, otherwise, the Mann–Whitney U test will be used to determine differences between the FtF and TR groups. Additionally, if the assumptions of normality are fulfilled, a repeated measures analysis of variance (RM-ANOVA) will be employed, otherwise, Friedman’s test will be used. Post hoc pairwise comparisons will be used to determine the intervention’s effect over time for each group (FtF and TR). Cohen’s d will be used to report effect sizes for the CoP variables. To allow repeated measures analysis, missing data will be adjusted by (1) replacing with the non-missing average values for each variable/week and (2) performing multiple imputations. Both methods will be used to make sure that the results are concordant. For all analyses, a *p*-value ≤ 0.05 will be considered statistically significant. All statistical analyses will be performed using IBM-SPSS 20.0 (SPSS Inc., Armonk, NY, USA).

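### The primary outcome, CoP sway area, is measured on eight postural tasks with none chosen as primary, every analysis is tested at 0.05, and the sample size allows for one comparison

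*Protocol article*

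**What the plan says.** All references are to the protocol article.

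- **Primary outcome (2.6.1).** CoP sway area, with no task and no visit named. The direction is given without restriction: "higher values of CoP_area_ signify suboptimal balance control".
- **Tasks (2.10).** "All primary and secondary posturographic measures will be evaluated across eight distinct postural tasks". Two are quiet standing, eyes open and eyes closed. For the rest, "six dynamic conditions will be evaluated: voluntary sway in the mediolateral direction" covers four (two metronome rates, each with eyes open and closed), and the last two are games: "Multidirectional sway will also be assessed while playing two different videogames".
- **Visits (2.6).** "Participants will be assessed at baseline, the ends of weeks 2, 4, and 6, and at weeks 8 and 10".
- **Analysis (2.11).** A t-test or Mann–Whitney test compares the groups. In addition there is a repeated-measures ANOVA or Friedman test, with post hoc comparisons over time within each group. None is called primary. The threshold is uniform: "For all analyses, a *p*-value ≤ 0.05 will be considered statistically significant".
- **Sample size (2.3).** One difference of 1.5 units, one SD of 1 cm², alpha 0.05, 80% power and 5% attrition, for a difference "between FtF and TR groups after six weeks that are clinically relevant". The result is 8 per group, 16 in total.
- **Design (2.1).** Non-inferiority. No margin is labelled as such.

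**The concern.** A trial sized for one comparison should say which comparison that is. Here the primary measure is one quantity on paper and eight in practice, and each may be declared significant at 0.05. Whoever reports the trial could present the most favourable task as the primary result and still comply with the text. For the non-inferiority aim the risk runs the same way: non-inferiority could be claimed from any task on which the telerehabilitation arm happened to look good.

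Direction is a second problem. A non-inferiority conclusion needs a defined unfavourable direction. In quiet standing, reading a larger area as poorer control follows the stated rationale. In a task that asks the participant to sway to a beat or to play a balance game, the area also reflects how far the person moved on purpose, and the article gives no reason why more movement should count as worse there.

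**Working it through.** **1. Count the primary measurements.** From 2.10: 2 static + 4 voluntary-sway + 2 game = 8 tasks, as stated.

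**2. Reproduce the sample size as a single comparison.** Inputs from 2.3: difference 1.5, SD 1, two-sided alpha 0.05, power 80%, attrition 5%.

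n per group = 2 × (1.960 + 0.842)² × 1² / 1.5² = 2 × 7.85 / 2.25 = 6.98, so 7. After attrition, 7 / 0.95 = 7.4, so 8 per group and 16 in total. This matches. A non-inferiority formula with 1.5 used as the margin and one-sided alpha 0.025 gives the same 7, then 8. Either way the figure contains no allowance for more than one test. The exact t-test power at 8 per group is 79.7%.

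**3. Chance of at least one false group difference across eight tasks at week 6, no adjustment.** If independent: 1 − 0.95⁸ = 0.337. The tasks are measured on the same people and will be correlated, but the article gives no correlation. Simulation of t-tests with 8 per arm and a common correlation (20,000 runs) gives:

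| Assumed correlation between tasks | At least one p ≤ 0.05 with no true difference |
|---|---|
| 0 | 34% |
| 0.3 | 30% |
| 0.5 | 26% |
| 0.7 | 20% |
| 0.8 | 16–17% |
| 0.9 | 12% |

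Even at 0.9 the error rate is more than twice the nominal 5%.

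**4. What keeping all eight as primary would cost.** With Bonferroni, alpha = 0.05 / 8 = 0.00625. Then n = 2 × (2.734 + 0.842)² / 2.25 = 11.4, so 12 per group; 12 / 0.95 = 12.6, so 13 after attrition. At the planned 8 per group, exact t-test power for a given task falls from 79.7% to 44.8%.

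**5. Illustration for the non-inferiority aim.** The protocol labels no margin, so this borrows 1.5 cm² only to show scale, with correlation 0.5 and one-sided 0.025. If the true deficit equals the margin on every task, the chance of a false claim on at least one of the eight is 13% instead of 2.5%. If there is no true difference and all eight tasks must succeed, power is 40% instead of 80%.

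**6. Direction.** Setting 2.6.1 beside 2.10, the larger-is-worse rule carries no limit, while 4 + 2 = 6 of the 8 tasks instruct movement. Neither section reconciles the two.

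**The case against.** The fair defence has several parts.

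- **Week 6 is implied.** Section 2.3 sizes the trial on the group difference after six weeks, and 2.11 handles time by repeated-measures methods with within-group post hoc comparisons. This stands. A reader might infer 8 × 5 = 40 between-group tests (87% if independent), but the text does not state a group test at each visit. Forty is only an upper bound.
- **A false difference is not a false non-inferiority claim.** Also correct. The figures in step 3 apply to the difference tests that 2.11 describes. Those in step 5 depend on a margin the protocol does not set.
- **A task hierarchy may exist in a fuller document.** Possible. But the article itself spreads the primary measure over eight tasks and fixes 0.05 for everything, so the point concerns what it states.
- **The direction rule is not shown to be wrong.** True. The article does not discuss direction by task. It is right to call the rule unjustified for the six dynamic tasks, but not to say that it reverses the result.

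Three further inferences also go too far. Snowboard and Penguin are training games as well as assessment tasks (2.5, 2.10), but both arms train on the same games for 18 sessions, so shared practice does not by itself bias the comparison between arms. Section 2.3 gives one SD and names no task; it does not say that 1 cm² applies to all eight. The metronome rates of 30 and 60 Hz look like a unit slip and have no bearing on which test is primary.

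**Conclusion.** The concern holds in this form: the article fixes no single primary test. Eight task-specific values of the primary outcome share a 0.05 threshold and a sample size built for one comparison. The firm count is eight tests at week 6, with a false-positive risk of 34% under independence, about 26% at correlation 0.5 and about 16–17% at 0.8. These figures assume unadjusted two-sided t-tests with 8 per arm and a common correlation that the documents do not supply. For non-inferiority, the open choice of task is the same weakness, but its size cannot be fixed without a stated margin. On direction, the supportable conclusion is that larger-is-worse lacks justification for six of the eight tasks.

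**What to change.** In 2.6.1 and 2.11:

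1. Name one static task, eyes open or eyes closed, chosen now, at week 6 as the single primary endpoint, with one named between-group analysis.
2. Make the other seven tasks and the other visits secondary or descriptive.
3. Limit the larger-is-worse rule to the static tasks, and state the favourable direction separately for the voluntary-sway and game tasks.

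As a minor side note, check and correct the metronome unit in 2.10.

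The cost is about a paragraph of text. No new data are needed, and the 8 per group still rests on one comparison. The real price is that favourable results on other tasks become supportive only. If the team prefers to keep all eight tasks as primary, it needs a stated multiplicity rule and a larger trial; Bonferroni would mean about 13 per group on the plan's own inputs.
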